### Sample size calculation

We calculated the sample size based on the primary efficacy endpoint. We assumed a transfusion rate of 90% in the Coagulogram-based group (i.e., control group) [11] and an absolute risk reduction of 25% for the Thromboelastometry-based and Restrictive groups. Using a study power of 0.80 and alpha of 0.05, we need *n* = 43 patients per group. The sample size was adjusted for multiple comparisons (additional increase of 20%, *n* = 8 per group) (Coagulogram-based versus Thromboelastometry-based, Coagulogram-based versus Restrictive, and Thromboelastometry-based versus Restrictive) according to Witte et al. [43]. To account for loss to follow-up, we have added 10% (*n* = 4) more patients to the adjusted sample size. The final required sample will be 55 patients per group (total estimated sample size of 165 patients).

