### Statistical analysis plan

All analyses will be performed as intention-to-treat. Categorical variables will be summarized as absolute and relative frequencies. Normality will be tested with the Kolmogorov-Smirnov test. Accordingly, continuous variables with normal distribution will be summarized as mean ± SD, or median and interquartile range (IQR) in case of non-normal distribution.

Comparisons between groups of continuous variables will be performed with one-way analysis of variance (one-way ANOVA) followed by Tukey’s test for multiple comparisons (for normally distributed variables), or the Kruskal-Wallis test followed by the Mann-Whitney *U* test (for non-normally distributed variables). Proportions between groups will be analyzed with the chi-square test or Fisher’s exact test, as appropriate.

All binary outcomes will be analyzed using a generalized linear model with binomial distribution and logit link function followed by pairwise comparisons adjusted by Bonferroni correction for multiple comparisons. Pairwise comparisons will be presented as odds ratio (OR) along with 95% confidence interval (95% CI), which will be calculated by logistic regression.

A survival curve will be performed with the Kaplan-Meier estimator and the log-rank test will be used to compare groups. To assess time-to-event (28-day mortality), an unadjusted Cox proportional hazards regression model will be performed. The hazard ratio (HR) with its respective 95% CI will be reported.

Prespecified subgroup analysis for the primary outcome will be presented as a Forest plot, and will include the presence of hypothermia (<35 °C), SAPS 3 score (≥50 points) and MELD score (≥25 points). Interaction between groups and each covariate will be assessed by multivariate logistic regression.

Two-tailed tests will be used and when *p* < 0.05, the test will be considered statistically significant. To account for multiple comparisons (Coagulogram-based versus Thromboelastometry-based, Coagulogram-based versus Restrictive and Thromboelastometry-based versus Restrictive), the α level will be adjusted to 0.0167.

We will make maximum effort to reduce missing data. We will use the multiple imputation method to handle missing data when necessary. The Statistical Package for the Social Sciences version 22.0 (IBM Inc., Chicago, IL, USA) will be used for statistical analyses. GraphPad Prism version 6.07 (GraphPad Software Inc., La Jolla, CA, USA) will be used for graph plotting.

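### Single-step Bonferroni at 0.0167 for all three pairs is valid but needlessly conservative with exactly three groups; a Shaffer stepwise rule keeps the 5% familywise error and gains power at no cost in patients

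*Protocol article*

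**What the plan says.** The Statistical analysis plan section of the Protocol article analyses all binary outcomes, which include the primary efficacy endpoint, with a three-group binomial logit model, "followed by pairwise comparisons adjusted by Bonferroni correction for multiple comparisons". Later in the section it names the three pairs (Coagulogram v Thromboelastometry, Coagulogram v Restrictive, Thromboelastometry v Restrictive) and says that "the α level will be adjusted to 0.0167". It describes no stepwise or closed procedure and gives no reason for the single-step choice. Pairwise odds ratios are reported with 95% intervals. On sidedness it says "Two-tailed tests will be used".

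The Sample size calculation section gives the assumptions: "We assumed a transfusion rate of 90% in the Coagulogram-based group", and "an absolute risk reduction of 25% for the Thromboelastometry-based and Restrictive groups". "Using a study power of 0.80 and alpha of 0.05", it arrives at 43 per group, adds 8 for multiple comparisons and 4 for loss to follow-up, and ends at 55 per group (165 in total).

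The section on data collection, monitoring and interim analysis plans two interim analyses, after 55 and 110 participants, with Lan-DeMets alpha spending.

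**The concern.** Single-step Bonferroni guards against three true null hypotheses at every step. With three groups that is necessary only for the first rejection. Any two pairwise equalities imply the third, so if one pair truly differs, at most one of the other two nulls can still be true. After the first rejection there is therefore nothing left to divide alpha between.

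What is at stake is power for each named comparison with control. The 20% enlargement for multiplicity does not bring power to 0.80 at the 0.0167 level, so the plan falls short of its own target under the method that it chose. The design also suits a stepwise rule. The Restrictive triggers (INR >5.0, platelets <25,000/μL) lie inside the control triggers (INR >1.5, platelets <50,000/μL, plus aPTT and fibrinogen). Restrictive v Coagulogram is thus the plausible first rejection, and Thromboelastometry v Coagulogram would then be tested at the less strict level. The article gives no distribution of INR or platelet counts from which to say how likely this is.

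**Working it through.** **Inputs** (Protocol article): control rate 0.90; both experimental rates 0.90 − 0.25 = 0.65; two-sided alpha 0.05; power 0.80; 1:1:1 allocation; 51 per group before and 55 after the allowance for loss; pairwise alpha 0.05/3 = 0.0167.

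**1. Reproduce the plan's base size.** With a pooled variance and no continuity correction,

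n = [z(α/2)·√(2p̄q̄) + z(β)·√(p₁q₁ + p₂q₂)]² / (p₁ − p₂)²

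Here p̄ = 0.775, √(2 × 0.775 × 0.225) = 0.5906 and √(0.09 + 0.2275) = 0.5635. At alpha 0.05: (1.960 × 0.5906 + 0.8416 × 0.5635)² / 0.0625 = 42.6, so 43. This matches the article, as do 43 + 8 + 4 = 55 and 3 × 55 = 165.

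**2. The same formula at 0.0167.** (2.394 × 0.5906 + 0.8416 × 0.5635)² / 0.0625 = 57.0, so 58 evaluable per group. That is 58/43 = 1.35, an increase of 35% where the plan adds 20%. Turning the formula round, power per control comparison is Φ[(0.25√n − 2.394 × 0.5906)/0.5635], which is 74.5% at n = 51 and 78.3% at n = 55.

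**3. Compare the two rules.** Simulation with 400,000 trials per scenario and a single look. Bonferroni tests every pair at 0.0167. Shaffer tests the smallest p-value at 0.0167 and, only if that succeeds, the other two at 0.05. True rates 90/65/65%:

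| Per group | Quantity | Test | Bonferroni | Shaffer |
|---|---|---|---|---|
| 51 | Power per control comparison | Pearson | 0.77 | 0.84 |
| 51 | Power per control comparison | logit Wald | 0.72 | 0.81 |
| 51 | Both reductions shown | Pearson | 0.64 | 0.78 |
| 51 | At least one reduction shown | Pearson | 0.90 | 0.90 |
| 55 | Power per control comparison | Pearson | about 0.79 | 0.87 |
| 55 | Power per control comparison | logit Wald | 0.77 | 0.85 |

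If the Restrictive rate were 40% (an assumption; the article plans 65%), then at 51 per group with Pearson tests Thromboelastometry v Coagulogram goes from 0.77 to 0.88, and Thromboelastometry v Restrictive from 0.55 to 0.75.

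**4. Familywise error of the Shaffer rule** (51 per group, Pearson): 0.042 with all rates 90%, 0.046 with all 65%, 0.049 at 90/90/65%, and 0.050 to 0.051 at 90/65/65%. At 55 per group and 90/65/65% it is 0.053, and the unadjusted Pearson test of the single true null has size 0.053 there too. The excess comes from the approximate test and not from the stepwise rule. The gate is essential: testing all three pairs at 0.05 without it gives about 0.12 when all rates are equal.

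**5. Why Shaffer is never less powerful.** Any p-value at or below 0.0167 means that the smallest p-value is too, so the gate is open and that pair is rejected. Every Bonferroni rejection is therefore also a Shaffer rejection.

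**The case against.** Bonferroni is a recognised method, the level 0.0167 is correctly derived, and familywise error is controlled. A reader might infer from this point that the analysis is wrong or that type I error is at risk. The document supports neither.

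A reader might also infer that the trial's main hypothesis is underpowered because of Bonferroni. The article hypothesises that the thromboelastometry-based and/or the restrictive protocol reduces transfusion. The chance of showing at least one reduction is about 0.90 under either rule, so the hypothesis read that way gains nothing. The gain is for each named comparison and for showing both.

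The shortfall is also modest at full enrolment. The primary endpoint is observed before catheterization, so few losses are to be expected, and with 55 per group Bonferroni already gives about 0.79 (Pearson) or 0.77 (Wald). The levels depend on the test, and the planned logistic model gives lower figures than Pearson in both columns.

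Bonferroni can supply matching simultaneous intervals, which a stepwise rule does not do simply. That advantage is real in general but unused here, because the plan reports 95% intervals and not 98.3% ones.

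The two interim looks mean that 0.0167 and 0.05 cannot simply be written in as fixed levels, and the figures above are for one look only. This shapes the wording of the fix but does not remove the gain.

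Finally, the text could be read as comparing Bonferroni-adjusted p-values with 0.0167, which would correct twice. The article does not say this is intended, so it calls for a clarifying word only.

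**Conclusion.** The point holds as a matter of efficiency. Single-step Bonferroni is valid, but with exactly three groups a Shaffer rule gives the same 5% familywise protection (apart from the approximation in the tests) and at least as much power in every scenario. At the planned rates the gain per control comparison is about 7 to 9 percentage points, which takes power from below the stated 0.80 to above it at both 51 and 55 per group and under both tests. For showing both reductions at 51 per group the gain is 14 points (0.64 to 0.78, Pearson). For showing at least one there is no gain.

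These figures rest on true rates of 90/65/65% and a single analysis. The article does not name the spending function, so the loss of power from the interim looks is not included for either rule.

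**What to change.** For the primary efficacy endpoint, replace the Bonferroni sentence with:

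> The three pairwise p-values are ordered. The smallest is tested at one third of the two-sided alpha available at that analysis under the Lan-DeMets spending function (0.0167 if all 0.05 were available). If it is significant, the other two are each tested at the full alpha available at that analysis; otherwise testing stops.

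The critical values at each look should come from the spending function run for each of these two shares of alpha. Add that the correction is applied once, and that the 95% intervals are descriptive.

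A closed test is a similar alternative: the three-group logit test first, then each pair at the same alpha. It is not identical to the Shaffer rule (0.845 against 0.839 per control comparison at 51 per group, Pearson), so one of the two should be named.

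The cost is a short amendment and no extra patients. The alternative of reaching 0.80 at 0.0167 needs 58 evaluable per group, in a trial whose Discussion names incomplete recruitment as a major issue. The downside is that intervals will not always agree with the stepwise decisions.

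Timing matters. Recruitment began in September 2014 and the article appeared in February 2017; at four patients a month, 29 × 4 = 116, so both interim looks may already have been reached. The change should be made and dated by people who have not seen comparative results. If that is no longer possible, Bonferroni should stay.

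### Pairwise odds ratios are given 95% intervals but tested at 0.0167, no risk difference with an interval is planned, and the odds ratio is not estimable if an arm has no major bleeding

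*Protocol article*

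**What the plan says.** **Design target (Sample size calculation).** The target is stated as two proportions and their difference: "We assumed a transfusion rate of 90% in the Coagulogram-based group (i.e., control group") and "an absolute risk reduction of 25% for the Thromboelastometry-based and Restrictive groups". The base size follows from "Using a study power of 0.80 and alpha of 0.05, we need" 43 per group. Additions of 8 for multiple comparisons and 4 for losses bring it to 55 per group.

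**Analysis (Statistical analysis plan).** All binary outcomes go into a binomial model with logit link, followed by Bonferroni-corrected pairwise comparisons. The format of the result is then fixed: "Pairwise comparisons will be presented as odds ratio (OR) along with 95% confidence interval (95% CI), which will be calculated by logistic regression". Further down, the general threshold is p < 0.05, and for the three pairwise comparisons "the α level will be adjusted to 0.0167". The section also says that categorical variables are summarized as counts and percentages, and that proportions are compared by chi-square or Fisher's exact test.

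**Endpoints (Study endpoints).** Both primary endpoints are binary: any transfusion before catheterization (efficacy) and major bleeding within 24 h (safety). Both therefore fall under the odds-ratio format.

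**The concern.** Three things in the prescribed format do not fit the rest of the plan.

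- **Level.** A two-sided test at 0.0167 pairs with a 98.33% interval. For any p-value from 0.0167 up to 0.05, a 95% interval excludes the null while the plan's rule declares no difference. Readers who go by the interval will reach the opposite conclusion.
- **Scale.** The design question is whether transfusion falls by 25 percentage points. No between-group estimate with an interval is planned on that scale, nor as a risk ratio.
- **Rare events.** The same model is prescribed for major bleeding, where an arm may have no events. The maximum-likelihood odds ratio is then zero or infinite and its Wald interval carries no information. Safety is part of the trial's hypothesis, so an interval for the bleeding difference is what a reader will look for.

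**Working it through.** **1. The plan's own figure.** Inputs from Sample size calculation: p1 = 0.90, p2 = 0.65, alpha 0.05, power 0.80. Tests are two-tailed (Statistical analysis plan). With pooled variance and mean rate 0.775:

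n = [1.960 × √(2 × 0.775 × 0.225) + 0.842 × √(0.90 × 0.10 + 0.65 × 0.35)]² / 0.25² = 42.6, rounded up to 43.

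This agrees with the plan, and 43 + 8 + 4 = 55. The trial was sized as a comparison of two proportions on the absolute scale.

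**2. The design effect on three scales.**
- Risk difference: 0.65 − 0.90 = −25 points.
- Risk ratio: 0.65 / 0.90 = 0.72, a 28% relative reduction.
- Odds ratio: (0.65/0.35) / (0.90/0.10) = 0.206, that is 79% lower odds.

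**3. The matching interval level.** 0.05/3 = 0.0167 and 1 − 0.0167 = 98.33%, with z = 2.394 against 1.960. The interval is 2.394/1.960 = 1.22 times as wide on the analysis scale. Wald intervals at the design rates with 55 per arm:

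| Measure | 95% | 98.33% |
|---|---|---|
| Odds ratio 0.206 | 0.073 to 0.584 | 0.058 to 0.736 |
| Risk difference −25.0 points | −39.9 to −10.1 | −43.2 to −6.8 |

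**4. A result where interval and test conflict.** Suppose 50/55 are transfused in the control arm and 41/55 in a comparison arm.
- Odds ratio = (41/14)/(50/5) = 0.293, log −1.228.
- Standard error = √(1/50 + 1/5 + 1/41 + 1/14) = 0.562.
- Wald z = −1.228/0.562 = −2.185, p = 0.029: not significant at 0.0167.
- 95% interval 0.10 to 0.88: excludes 1.
- 98.33% interval 0.08 to 1.12: includes 1.

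**5. How often.** Binomial probabilities were summed over all tables with 55 per arm whose Wald p-value lies from 0.0167 up to 0.05, leaving out tables with a zero cell. Per comparison:

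| True rates | Chance of conflict |
|---|---|
| 90% vs 65% | 13% |
| 90% vs 75% | 21% |
| 90% vs 90% | 2% |
| 65% vs 65% | 4% |

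**6. Empty arms for major bleeding.** The article gives no expected rate of major bleeding. Its Background cites 12 to 94 bleeding events per 1000 catheter insertions. As an assumption, take a common rate p within that range. The chance that at least one of three arms of 55 has no event is 1 − [1 − (1 − p)^55]³:

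| Assumed p | (1 − p)^55 | At least one empty arm |
|---|---|---|
| 1.2% | 0.515 | 89% |
| 3% | 0.187 | 46% |
| 5% | 0.060 | 17% |
| 9.4% | 0.004 | 1% |

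**7. A risk difference still works there.** Take 0/55 against 2/55 as an illustration. The 98.33% Wilson limits are 0 to 9.4% and 0.8% to 15.2%. Newcombe's limits for the difference of −3.6 points are:
- lower: −3.6 − (15.2 − 3.6) = −15.2 points;
- upper: −3.6 + √(9.4² + (3.6 − 0.8)²) = +6.2 points.

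The odds ratio for the same table has no finite logarithm.

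**The case against.** Four objections deserve an answer.

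**Percentages will be shown.** A reader might infer that the odds ratio is all the trial will report. The document does not support that. Counts and percentages by arm are promised, so the point difference follows by subtraction and can be set against 25 points. What is absent is a between-group difference or risk ratio with its own interval.

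**The odds ratio is not wrong.** One might also say that it overstates the effect. But 0.21 is the correct odds ratio for 65% against 90%; it misleads only when read as a risk ratio, and nothing in the article reads it so. Sizing on proportions and analysing by logistic regression is ordinary practice and undermines neither the test nor the sample size. This objection stands, and the scale point is therefore one of interpretability.

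**The intervals might already be adjusted.** The sentence before the quoted one applies Bonferroni to the pairwise comparisons, so simultaneous intervals could be meant. The quoted sentence, however, says 95% from logistic regression with no mention of adjustment. The literal reading is an unadjusted interval, and at best the text is ambiguous.

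**Fisher's test covers empty arms.** It does give a valid comparison, so the stronger claim that the safety analysis fails is not supported. It is planned as a test only, and the one prescribed estimate with an interval is the one that breaks down.

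**Conclusion.** The point holds as a mismatch in how results are to be reported. It does not put the validity of the primary test or the design in question.

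- **Interval against test:** on the literal wording, about a 13% chance of conflict per comparison at the design rates, 21% if the true reduction is 15 points, and 2% to 4% with no difference. This assumes 55 analysed per arm, Wald tests and intervals from the logistic model, and a final level of 0.0167.
- **Scale:** no planned interval can be compared directly with the 25-point target, and the odds ratio of 0.21 is open to being misread beside a risk ratio of 0.72.
- **Major bleeding:** the chance that at least one arm is empty runs from 1% to 89% over assumed rates of 9.4% down to 1.2%. The size of this part depends wholly on that rate, which the document does not give.

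**What to change.** In the Statistical analysis plan:

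1. For both primary endpoints, report each pairwise risk difference with a Newcombe or Miettinen-Nurminen interval, and keep the odds ratio beside it. Where an arm has no events, state that the odds ratio is not estimable and rely on the risk difference.
2. Set the interval level to the alpha at which the comparison is finally judged: 98.33% if 0.0167 stands. Data collection, monitoring and interim analysis plans two interim looks with Lan-DeMets spending. If these lower the final level for the primary comparisons, raise the interval level accordingly. Say explicitly that the intervals are adjusted.
3. State which test decides each pairwise comparison, since both chi-square or Fisher and the logistic model are named. A matched level alone does not guarantee agreement near the boundary. For 50/55 against 40/55, the logistic Wald z is ln(0.267)/0.558 = −2.37 (p = 0.018). The chi-square version is −0.182/√(0.818 × 0.182 × 2/55) = −2.47 (p = 0.013). These fall on opposite sides of 0.0167.

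The cost is a few sentences, one extra column in the results table and intervals about 1.22 times as wide as at 95%. No change to data collection, randomization or sample size is needed. Recruitment was ongoing when the article appeared, so the wording could be settled before the final analysis.

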### Costs analysis

Transfusion and laboratory test costs will be assessed. For the analysis of the costs of laboratory tests, we will include the total cost of the test(s) (i.e., ROTEM® or SCTs), which will guide the blood transfusion. The unit cost information regarding blood products and coagulation tests will be obtained from the blood bank and main laboratory of Hospital Israelita Albert Einstein.

### Ethics

The study was designed in accordance to the Declaration of Helsinki. The Hospital Israelita Albert Einstein Ethics Committee approved the study on 12 August 2014 (reference number: 734824). Recruitment of participants started in September 2014 and is currently ongoing. The study was registered at ClinicalTrials.org (identifier: NCT02311985) on 3 December 2014. The research team will release the study results in scientific media regardless of their final results.

A trained research team member will obtain the informed consent term from the research subject or their next of kin. A deferred informed consent term will be applied in case of emergency CVC when the patient lacks clinical condition and no next of kin is immediately available. In this case, the definitive informed consent must be obtained within 24 h after the procedure. The participants may leave the study at any time with no treatment disadvantage. All study information will be kept secured with limited access. The patient database will be password-protected and patients will be identified by trial ID numbers. A translated copy of the Informed Consent Form is available (see Additional file 2).

## Discussion

Our trial is designed to compare three protocols to guide transfusion of blood components prior to CVC in critically ill patients with chronic liver failure. We hypothesized that restricted and thromboelastometry-guided transfusion protocols would be safe and significantly reduce empirical transfusion of blood products in cirrhotic critically ill patients. By reducing transfusion rates, these strategies would also reduce transfusion-related complications and costs. This would help to provide quality evidence for reduction of empirical transfusion of critically ill patients with coagulopathy in clinical practice.

One main focus of our trial is that the transfusion protocols used are based on a comprehensive assessment of coagulation, which includes the contribution of coagulation factors, platelets and fibrinogen. Most randomized trials published so far have relied on a specific aspect of coagulation and a specific blood product transfusion (e.g., FFP transfusion according to PT/INR) [48, 49]. Furthermore, fibrinogen is one of the most important coagulation factors [50], and we believe that including the evaluation of hypofibrinogenemia or dysfibrinogenemia would result in a more detailed understanding of coagulation status and, therefore, help in further prevention of bleeding. Additionally, we will use wide inclusion criteria, accounting for emergency insertions, active bleeding and use of antiplatelet aggregation agents making the case-mix of patients more similar to critical care practice.

We considered the use a restrictive blood transfusion protocol to be of vital importance. Several series of observational studies that included patients with coagulopathy have shown that experienced inserters have low complication rates in different populations of patients with coagulopathy, even when no blood transfusion is performed prior to the procedure [51–55]. A large meta-analysis showed that real-time ultrasound guidance for CVC significantly reduced failure to obtain central venous access, arterial puncture, hematoma formation and hemothorax by 82%, 75%, 70% and 90%, respectively, when compared to using anatomical landmark guidance [56]. Those positive effects are extended to hemodialysis catheters [57]. Furthermore, the use of real-time ultrasound guidance increases the success rate in the first attempt [6]. These may reduce complication rates to a minimum, even in patients with coagulopathy. We believe that blood product transfusion is frequently excessive when a trained inserter in ultrasound-guided CVC performs the procedure.

We have foreseen some potential issues for this trial. One major issue is not to complete the necessary recruitment required due to low adhesion by practicing physicians and the single-center setting. Every practice-changing protocol may be prone to resistance and low adhesion, mainly by cultural environment. Conversely, we will use broad inclusion criteria and health care provider sensitization campaigns to try to overcome this potential drawback. Another issue is an early trial stop due to either efficacy or harm. We programmed two interim analyses when one third and two thirds of patients are enrolled, respectively. Since few randomized clinical trials have assessed restrictive blood transfusion protocols prior to invasive procedures in critically ill patients with cirrhosis, we will follow the research subjects closely for adverse events.

This trial has potential limitations. Single-center trials may have a potential limited external validity [58] and may overestimate treatment effect when compared to multicenter trials [59]. The results from single-center trials must be applied with caution in daily clinical practice. This trial is not adequately powered to address transfusion-related complications, which ranges from one event in hundreds to thousands of blood transfusions [60]. Accordingly, our primary objective is to evaluate the feasibility and safety of strategies that use a more detailed overview of coagulation status or restrictive transfusion of blood components in critically ill patients with cirrhosis.

The results from this trial will help to develop multicenter randomized clinical trials to assess blood product transfusion prior to invasive procedures in critically ill patients with suspected coagulopathy. Our intention is to provide good-quality scientific evidence for transfusion of blood products in patients with coagulopathy, reducing excessive and empirical use of blood and costs in the health care system.

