Rotational thromboelastometry (ROTEM®) is a point-of-care test that evaluates coagulation according to the viscoelastic properties of a whole blood sample [26]. ROTEM® has the advantage of a more comprehensive (clot initiation, formation and stabilization) and faster (online) bedside coagulation evaluation when compared to SCTs [27]. Clinical protocols based on thromboelastometry have been effective in reducing blood transfusion, costs and mortality in diverse clinical settings [28–31] including liver transplantation [32, 33].

General clinical practice guidelines recommend prophylactic transfusion of blood products prior to invasive procedures based on SCTs alterations [34–36]. Nevertheless, there is no consensus as to whether and how blood transfusion should be used before invasive procedures, particularly in patients with cirrhosis. The majority of available data have originated from small clinical trials and observational studies, which limit an evidence-based approach. The culture of blood transfusion is moving towards a rational evidence-based use of blood and its components [37].

This study will compare three blood transfusion protocols (coagulogram-based, thromboelastometry-based and restrictive) prior to CVC in critically ill patients with cirrhosis. We hypothesized that restrictive and/or thromboelastometry-guided transfusion protocols are safe and would decrease the need of blood products transfusion compared to an ordinary coagulogram-based protocol in critically ill patients with cirrhosis submitted to a CVC.

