## Methods/design

### Study design

This is a double-blinded, parallel-group, superiority, single-center, randomized controlled clinical trial.

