### Study endpoints

The primary efficacy endpoint is the proportion of patients transfused with any blood product (i.e., FFP, platelets or cryoprecipitate) prior to CVC. The primary safety endpoint is the incidence of major bleeding within the first 24 h after catheter insertion. Major bleeding was defined according to the HEME tool [41]. According to the HEME tool, major bleeding is defined as overt bleeding with any of the following (in the absence of other causes): decrease in hemoglobin of 20 g/L or more, transfusion of 2 or more units of RBC with no increase in hemoglobin level, decrease in systolic BP by 10 mmHg or more while the patient is sitting up, spontaneous decrease in systolic BP of 20 mmHg or more or increase in heart rate by 20 bpm or more; bleeding at any one of the following sites: intracranial, intraspinal, intraocular, pericardial, retroperitoneal or intraarticular; or wound-related bleeding requiring an intervention.

The secondary efficacy endpoints will be: the proportion of patients transfused with each blood component and the infused volume of each blood component, hemoglobin and hematocrit levels before and up to 24 h after CVC, costs associated to blood product transfusion and laboratory tests, ICU and hospital length of stay, and ICU, 28-day and hospital mortality. Secondary safety endpoints will include: the incidence of minor bleeding complications (i.e., oozing or hematoma with no criteria for major bleeding) and the proportion of patients transfused due to bleeding within the first 24 h after CVC, and the incidence of acute transfusion-related adverse events (i.e., transfusion-associated cardiac overload, acute hemolytic transfusion reactions, anaphylactic reactions, febrile nonhemolytic reactions and urticarial reactions). The transfusion of bleeding patients after CVC will follow the Hospital Israelita Albert Einstein institutional transfusion protocol. Accordingly, if INR >1.5 or aPTT >32 s, FFP (10 mL per kg) is administered. If serum fibrinogen <150 mg/dL, cryoprecipitate (1 unit per 10 kg) or fibrinogen concentrate (2 to 4 g) is administered. If the platelet count <50 x 10^3^/mm^3^, random platelets (1 unit per 10 kg) or apheresis platelets (1 unit) are administered. Correction of hypothermia (axillary temperature ≥35 °C), hypocalcemia (ionized calcium ≥1.14 mmol/l) and acidosis (pH ≥7.31) is always recommended.

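### The protocol hypothesises that the new transfusion strategies are safe, but its analyses of major bleeding (difference tests and logistic odds ratios in a sample sized for transfusion) cannot support a conclusion of safety

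*Protocol article*

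**What the plan says.** All references are to the protocol article.

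- **Aim.** Background: "We hypothesized that restrictive and/or thromboelastometry-guided transfusion protocols are safe and would decrease the need of blood products transfusion". The abstract and the opening of the Discussion repeat the safety hypothesis. The limitations paragraph of the Discussion adds that "our primary objective is to evaluate the feasibility and safety of strategies".
- **Endpoint.** Study endpoints: "The primary safety endpoint is the incidence of major bleeding within the first 24 h after catheter insertion", defined by the HEME tool.
- **Framework.** Study design: "This is a double-blinded, parallel-group, superiority, single-center, randomized controlled clinical trial". No non-inferiority or equivalence comparison is named.
- **Size.** Sample size calculation: "We calculated the sample size based on the primary efficacy endpoint". The inputs are all about transfusion: "We assumed a transfusion rate of 90% in the Coagulogram-based group" and "an absolute risk reduction of 25% for the Thromboelastometry-based and Restrictive groups".
- **Analysis.** The Statistical analysis plan section handles every binary outcome alike: chi-square or Fisher's exact test, then a logit-link binomial model with Bonferroni-adjusted pairwise odds ratios and 95% CIs. Tests are two-tailed, with α set to 0.0167 for the three comparisons.
- **Limitation admitted.** The Discussion concedes inadequate power for transfusion-related complications. It says nothing of the kind about bleeding.

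**The concern.** Safety here means that withholding products does not cause an unacceptable excess of bleeding. That claim needs evidence that rules out an excess. A superiority test asks the opposite question, and failing to reject no difference does not rule out harm.

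The one stated power limitation concerns transfusion reactions, a harm that the new strategies are expected to reduce. Bleeding, the harm that less transfusion might increase, is left out, and the next sentence turns to safety as the primary objective.

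At stake is what the trial may conclude on its primary safety endpoint. With few or no bleeds per arm, the planned test will almost never be significant and the planned effect measure may not exist.

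**Working it through.** **1. The plan's own figure.** Inputs from Sample size calculation: 90% against 65% transfused, power 0.80, α 0.05. With pooled variance, two-sided, no continuity correction:

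n = [1.96·√(2·0.775·0.225) + 0.8416·√(0.90·0.10 + 0.65·0.35)]² / 0.25² = (1.1575 + 0.4742)² / 0.0625 = 42.6, so 43 per group.

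This matches the article. Its additions give 43 + 8 + 4 = 55. No bleeding quantity enters.

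**2. What a difference test can miss at 55 per arm.** For 6/55 against 0/55, the two-sided Fisher p is

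2 × (55·54·53·52·51·50)/(110·109·108·107·106·105) = 2 × 0.01353 = 0.027.

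That is above 0.0167. The expected number of bleeds per arm is 6 × 55/110 = 3, below the usual threshold of 5, so Fisher's test is the appropriate one of the two that the plan allows. The choice matters: the uncorrected chi-square is 110·(6·55)²/(55·55·6·104) = 6.35, p = 0.012. With Fisher's test, 7/55 (12.7%) against 0/55 is needed to pass 0.0167.

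**3. Power for a doubling (assumed rates).** The article gives no major-bleeding rate. Background gives 12 to 94 per 1000 insertions for any catheter bleeding, used here only to span control rates. Fisher power at 55 per arm, by enumeration:

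| Control → new | α 0.05 | α 0.0167 |
|---|---|---|
| 1.2% → 2.4% | 0.1% | 0.02% |
| 5% → 10% | 7.5% | 4.0% |
| 9.4% → 18.8% | 20% | 11% |

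**4. Whether the odds ratio exists.** With no bleeds in an arm, the maximum-likelihood odds ratio is zero, infinite or undefined, and the usual interval fails. P(no bleeds in an arm) = (1 − p)^55:

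- p = 1.2%: 0.988^55 = 0.51
- p = 2%: 0.98^55 = 0.33
- p = 9.4%: 0.906^55 = 0.004

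If both arms of a comparison share the rate, the chance that at least one is empty is 1 − (1 − 0.515)² = 0.76 at 1.2% and 1 − (1 − 0.329)² = 0.55 at 2%.

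**5. What a risk-difference interval would show.** Newcombe's method combines the two Wilson intervals. For 0/55 the Wilson upper limit is z²/(n + z²) = 3.84/58.84 = 6.5%. For 1/55 (1.8%) the Wilson limits are 0.3% and 9.6%. With difference = new minus control:

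- 0/55 against 0/55: upper limit √(6.5² + 0²) = +6.5 points
- 1/55 against 0/55: upper limit 1.8 + √((9.6 − 1.8)² + 0²) = +9.6 points
- 0/55 against 1/55: upper limit −1.8 + √(6.5² + (1.8 − 0.3)²) = +4.9 points
- 0/55 against 3/55: upper limit +2.0 points

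All four intervals are finite, including those with empty arms.

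**The case against.** **The article never equates non-significance with safety.** A reader might infer that a p above the threshold will be declared safe. No section says so: *safe* is a hypothesis, and the objective is to evaluate safety. This objection stands. What remains is that the article states a safety hypothesis and no criterion for judging it.

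**Intervals are already planned.** Correct: pairwise odds ratios come with 95% CIs, so it would be wrong to say that only a test is planned. But these intervals fail when an arm is empty, and no bound is set to read them against.

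**The article is cautious elsewhere.** It urges care with single-center results, names feasibility beside safety, points to later multicenter trials and has an independent DSMB that can recommend stopping for harm. This softens the picture, but none of it defines what would count as safe.

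**Major bleeding may not be rare.** The HEME definition is broad, and no rate is given. This is fair, and the empty-arm problem nearly disappears at 9.4%. Power for a doubling is still at most 20% there. The two ends of the quoted literature range should not be set against each other as if they were trial arms: they come from different sources and describe any bleeding.

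**Sizing on efficacy is conventional, and a bound could sit in an unseen SAP.** Both points are fair, so the absence of a non-inferiority margin is not itself the fault. The design framework, basis of size, planned measure and limitation wording are all stated in this article.

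**Conclusion.** The point holds in this form: the stated analyses of major bleeding cannot support a conclusion that the restrictive or thromboelastometry strategy is safe. At 55 per arm, a 10.9-point observed excess (6/55 against 0/55) is not significant at 0.0167 by Fisher's test. The planned odds ratio has about a 51% chance per arm of meeting a zero count at 1.2%, or 33% at 2%. Those rates are assumptions; the Fisher result and the intervals depend only on counts and arm size, taken as the full 55.

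A reader might also infer from the 0 against 0 result that this sample can never exclude an excess below 6.5 points. That is not so: fewer bleeds in the new arm than in control gives tighter limits, such as +4.9 or +2.0 points. The 6.5 and 9.6 figures illustrate particular outcomes only.

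This is a matter of analysis and wording, and should be corrected. It does not call for a larger trial.

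**What to change.** 1. For each new strategy against Coagulogram, report the major-bleeding risk difference with a 95% interval that is valid at zero counts, such as Newcombe's, in place of the logistic odds ratio as the main measure.
2. State that a non-significant difference will not be taken as evidence of safety, and word the conclusion by the excess that the interval excludes.
3. If an acceptable excess is to be used, have it fixed by people blinded to bleeding by arm. Otherwise call the safety comparison descriptive. Blinding matters because recruitment began in September 2014 at a quoted four per month. If that rate held to publication in February 2017, about 29 × 4 = 116 patients were enrolled, past both interim looks (55 and 110), so DSMB members may already have seen bleeding by arm.
4. Add major bleeding to the underpowered outcomes in the limitations paragraph of the Discussion.

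The cost is a change to analysis and limitations wording, with no extra patients or data. The downside is a weaker permitted safety claim.
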